### 2.13. Anticipated Dates of Trial Commencement and Completion

The trial is scheduled to commence in October 2022, and completion is scheduled for June 2023. Currently, the RCT has not yet started.

### 2.14. Sample Size Calculation

The estimation of the sample size was performed with the use of the G*Power, version 3.1 program. For a three parallel groups design involving three repeated measures (pre, post-treatment, and one follow-up), in order to achieve a statistical power of 0.80 in detecting a medium effect size (Cohen’s f = 0.25) in the interaction effect, at a significance level of 5% (0.05), it was calculated that a minimum sample size of 80 individuals would be required. Taking into consideration a dropout rate of 10%, it was estimated that 30 individuals per group would need to be initially recruited [21].

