## 4. Conclusions

This randomized controlled trial will determine the effectiveness of cervical and diaphragmatic manual therapy, plus breathing reeducation exercises, in NSCNP patients. The present study is expected to have high internal validity, since this protocol is planned according to accepted methodology regarding the randomization, concealed allocation, blinding of examiners, intention-to-treat analysis, and appropriate sample size calculation. This study is innovative, as it combines the mobilization of the cervical spine with diaphragmatic mobilization and breathing reeducation exercises, to address the rehabilitation of patients with NSCNP in a more comprehensive manner. 

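### The minimum sample size of 80 is not reproduced by the stated three-group, three-time design under any standard G\*Power option at sphericity, and it equals a two-group result

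*Protocol article*

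**What the plan says.** Section 2.14 names the software: "The estimation of the sample size was performed with the use of the G*Power, version 3.1 program". The design is given as "For a three parallel groups design involving three repeated measures (pre, post-treatment, and one follow-up"). The aim is described as "detecting a medium effect size (Cohen’s f = 0.25) in the interaction effect", with the power set to 0.80 and alpha to 0.05. The result is that "it was calculated that a minimum sample size of 80 individuals would be required". The recruitment figure follows: "Taking into consideration a dropout rate of 10%, it was estimated that 30 individuals per group would need to be initially recruited".

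Section 2.5 allocates patients to three arms in blocks of three, so the arms are equal. Section 2.15 plans a two-way mixed ANOVA that looks at the group-by-time interaction, so the effect used for sizing is the effect to be tested. Section 4 lists an "appropriate sample size calculation" among the reasons to expect high internal validity.

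Section 2.14 does not state the effect-size option, the correlation among repeated measures or the nonsphericity correction (epsilon).

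**The concern.** A total of 80 is an odd result for three equal arms, because it is not a multiple of three. For a within-between interaction, the program's answer depends on the number of groups through the degrees of freedom, so entering the wrong number changes the sample size. Section 2.14 is the only justification given for the size of the trial, and the conclusions rely on it. If the printed figure belongs to another design, the stated power of 0.80 for a medium interaction is not the power this trial has.

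**Working it through.** **Inputs.** From section 2.14: k = 3 groups, m = 3 measurements, f = 0.25 (so f² = 0.0625), alpha = 0.05, power 0.80, stated minimum N = 80, dropout 10%. From section 2.5: equal arms. Assumed, because not stated: epsilon = 1 (sphericity) and, where the option needs a correlation, rho = 0.5. Both are varied below.

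**Formulas.** Power is the upper tail of a noncentral F distribution beyond the central 5% critical value, with

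- df1 = (k − 1)(m − 1)ε
- df2 = (N − k)(m − 1)ε

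The noncentrality λ depends on the effect-size option:

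- default: λ = f²·N·m·ε/(1 − rho)
- as in Cohen: λ = f²·N·(m − 1)·ε
- as in SPSS: λ = f²·(N − k)·(m − 1)·ε

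**Step 1: the plan's own figure.** Two groups, three times, Cohen option: df1 = 1 × 2 = 2.

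- N = 79: df2 = 154, λ = 0.0625 × 79 × 2 = 9.875, power 0.802. This is the smallest N that reaches 0.80.
- N = 80 (two equal groups): df2 = 156, λ = 10.0, power 0.807.

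This gives the printed 80 exactly.

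**Step 2: the stated design.** Three groups, three times, ε = 1: df1 = 2 × 2 = 4.

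| Option | Smallest N | N for equal arms | λ at that N | Power at that N | Power at 80 | Power at 90 |
|---|---|---|---|---|---|---|
| Default, rho 0.5 | 35 | 36 | 0.0625 × 36 × 3/0.5 = 13.5 | 0.823 | 0.996 | above 0.99 |
| As in Cohen | 98 | 99 | 0.0625 × 99 × 2 = 12.375 | 0.805 | 0.701 | 0.760 |
| As in SPSS | 101 | 102 | 0.0625 × 99 × 2 = 12.375 | 0.805 | 0.682 | 0.744 |

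None of the three gives 80. Under the Cohen option at N = 80, λ is 10.0, the same as in step 1. Power falls from 0.807 to 0.701 because df1 rises from 2 to 4.

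**Step 3: detectable effect.** Under the Cohen option with three groups, 80% power is reached at f = 0.277 with 80 completers and f = 0.261 with 90.

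**Step 4: can unstated settings give 80 with three groups?** Using the default option:

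| rho | ε | N for equal arms | Power at 80 |
|---|---|---|---|
| 0 | 1 | 69 | 0.880 |
| −0.2 | 1 | 81 | 0.807 |
| 0 | 0.75 | 81 | 0.799 |
| 0.25 | 0.5 | 81 | 0.799 |

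At sphericity, the largest N for any non-negative correlation is 69. Reaching 81 takes a negative correlation, or a low correlation together with a marked sphericity penalty.

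**Step 5: dropout.** 80/0.9 = 88.9, rounded up to 89, then to 90 for three equal arms. This step is consistent.

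**The case against.** The strongest objection is that section 2.14 does not state three of the settings that determine the answer, and a condensed journal article may leave such settings to a fuller document. Without them, 80 can be neither derived nor refuted outright. Step 4 shows three-group inputs that give 81, and with those the claimed power holds to rounding (0.799 at 80, about 0.85 at 90). Under the default option with rho 0.5 the trial is larger than it needs to be. All of this stands. It limits the finding to a mismatch under ordinary settings plus a probable cause. The missing settings are not in themselves the complaint. The complaint is that a printed total disagrees with the printed design under each standard option at sphericity.

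Two stronger readings are tempting. A reader might infer that the trial is shown to be underpowered, at 0.70. The document does not support that, because 0.70 holds only if the Cohen option was used. A reader might also infer that the calculation fails because it does not power the three pairwise comparisons. That does not follow either: section 2.14 sizes the interaction, and section 2.15 tests the interaction and turns to post hoc tests only if it is significant. Powering the pairwise contrasts would be a different design choice, not a correction of an error.

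**Conclusion.** The point holds as a mismatch between a stated figure and its stated design. For three groups, three times and an interaction of f = 0.25, the standard options at sphericity give 36, 99 or 102 (the first with rho 0.5), not 80. The exact match with the two-group Cohen calculation, together with a total that three does not divide, makes a two-group entry the likely explanation. It remains an inference.

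The consequence depends on the option used. Under the Cohen option, three groups would need 99 completers for power 0.80; with 80 completers power is about 0.70, and with 90 about 0.76. Under the default option with a positive correlation and no large sphericity penalty, power at 80 exceeds 0.80. As written, the stated power of 0.80 cannot be relied on in either direction. The arithmetic is certain; the diagnosis of the cause is probable.

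**What to change.** Keep the 90 patients. Re-run the calculation with three groups and three measurements, and rewrite section 2.14 to state the number of groups entered, the effect-size option, the correlation among repeated measures and epsilon. Then restate the power that the trial has:

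- If the Cohen option was used: about 0.70 at 80 completers and 0.76 at 90, with 80% power for f of about 0.28 and 0.26 respectively.
- If the default option with a positive correlation was used: the smaller minimum N and the higher power that it gives.
- If atypical three-group inputs were used: those inputs with a reason for them, and 81 as the total for equal arms.

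The sentence in section 4 on the sample size calculation should then agree with the restated figure. Adding a pairwise detectable difference is optional. The cost is one rewritten paragraph and possibly a less favourable power figure. No change to recruitment or to the planned test follows, and section 2.13 says that the trial has not yet started.

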### 2.15. Statistical Analysis

Baseline characteristics and all outcome measurements will be analyzed initially in each group for normality of their distribution using the Shapiro–Wilk Test. Descriptive statistics will be used to present the distribution of the data.

Statistical analysis for the RCT will be conducted, based on intention-to-treat analysis. In this way, the individuals will be analyzed in the groups in which they were randomly allocated. A separate analysis will be conducted in case any protocol deviations occur for part of the population, such as low adherence with the organized treatment sessions, low home compliance (<50% attendance), or should patients withdraw themselves from the RCT. Linear mixed models (two-way mixed ANOVA) with one repeated measures factor (time) and another between-groups factor (group), especially considering the interaction between the factors of time (week 0, week 4, and week 16) and group (A and B, A and C, B and C). Additionally, post hoc tests will be employed to determine the source of the interaction, if significant. 

The principal components analysis method will be performed for the factor analysis of the NQ. Pearson’s bivariate correlations will be employed for the examination of concurrent validity of respiratory outcomes.

For all analyses, a significance level of 5% will be considered. All data processing will be performed using the IBM SPSS software, version 28. 

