### 2.12. Interventions

Ten treatment sessions will be administered to all participants, thrice for the first two weeks and twice for the third and fourth weeks, lasting for 40 min per session. The sessions will be individually administered in a reserved room with adequate lighting, music, and air conditioning. 

The manual therapy program will be applied by a physical therapist (main researcher), a clinical instructor of manual therapy, PhD candidate, with an OMT diploma from a recognized IFOMPT program, certified as Mulligan Practitioner, with two Master of Science degrees from the Athens Medical School, Greece, and 20 years of experience in clinical practice. A physical therapist with a Master of Science degree from the Athens Medical School and 17 years of experience in clinical practice will administer the traditional physiotherapy program (Group C) and the sham diaphragmatic manual therapy component (Group B). Sham diaphragmatic manual therapy will be administered via a therapeutic ultrasound device [43]. 

The participants can only receive the assigned treatment. They will be advised against combining the treatment they were allocated to with medication or other physical therapy approaches. Any deviation from the treatment sessions administration (missing more than one appointment) or any worsening of symptoms will be reasons for exclusion. The interventions proposed for each group are described briefly below, and in detail in the Supplementary Materials. All selected interventions are widely applied in the field of physical therapy and are safe when administered by appropriately trained physical therapists. 

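### The main model takes week 0 as a repeated outcome, forgoing the precision of baseline adjustment, and its double name leaves open whether patients with a missing visit are kept

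*Protocol article*

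**What the plan says.** Section 2.15 of the protocol article describes the analysis of the trial outcomes as "Linear mixed models (two-way mixed ANOVA) with one repeated measures factor (time) and another between-groups factor (group", with attention on "the interaction between the factors of time (week 0, week 4, and week 16) and group". The group pairs listed are A and B, A and C, and B and C. Post hoc tests follow if the interaction is significant. The software is SPSS 28; no procedure is named.

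The same section states the principle: "Statistical analysis for the RCT will be conducted, based on intention-to-treat analysis". It explains this as meaning that "the individuals will be analyzed in the groups in which they were randomly allocated". For withdrawals and low adherence it adds: "A separate analysis will be conducted in case any protocol deviations occur for part of the population".

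Two other sections bear on incomplete data. Section 2.14 inflates the sample size: "Taking into consideration a dropout rate of 10"%. Section 2.12 lists post-randomisation events, "missing more than one appointment) or any worsening of symptoms will be reasons for exclusion".

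**The concern.** There are two issues, of different weight.

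**Baseline.** Week 0 is measured before treatment, so randomisation makes the group means equal there in expectation. A model that gives each group its own week-0 mean ignores this. Its interaction contrasts become differences in change from baseline, which carry more noise than differences adjusted for the baseline value. The trial collects that value anyway, so the lost precision could be recovered without more patients or visits.

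**Model name.** A linear mixed model and a two-way mixed ANOVA give the same interaction test when data are complete and the covariance is compound symmetric. They part when a visit is missing. A repeated-measures ANOVA drops the whole patient, whereas a likelihood-based mixed model uses the visits that exist. Writing one as a gloss on the other leaves the analysed population open in a trial that promises intention-to-treat and expects dropout.

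**Working it through.** **The plan's own figures.** Section 2.14 gives 80 as the minimum and 30 per group as recruited. The dropout step reproduces: 80/0.9 = 88.9, so 89, rounded up to 90 in three equal groups. The 80 itself cannot be reproduced from the stated inputs (f = 0.25, power 0.80, alpha 0.05, three groups, three measurements), because the correlation among measurements and the sphericity correction are not given. With correlation 0.5 and no correction the same calculation gives 35; with correlation 0 and a correction of 0.75 it gives 81. The point made here does not depend on this.

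**Precision: inputs.** Per arm n = 30 × 0.9 = 27 (section 2.14). Outcome SD is set to 1 at each visit. The correlation r between baseline and follow-up is not in the article, so 0.3, 0.5 and 0.7 are assumed. The pairwise difference of 0.65 SD is an illustration.

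**Formulas, per patient, at one follow-up visit.**
- Change from baseline: variance 2(1 − r).
- Baseline-adjusted: variance 1 − r².
- Ratio of adjusted to change: (1 − r²) / [2(1 − r)] = (1 + r)/2.
- Power: two-sided two-sample t test at 5%, 52 degrees of freedom, noncentrality (0.65/s) × √(27/2), where s is the square root of the variance. The single degree of freedom spent on the covariate is ignored.

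| r | Change variance | Adjusted variance | Reduction | Noncentrality, change / adjusted | Power, change / adjusted |
|---|---|---|---|---|---|
| 0.3 | 1.40 | 0.91 | 35% | 2.02 / 2.50 | 51% / 69% |
| 0.5 | 1.00 | 0.75 | 25% | 2.39 / 2.76 | 65% / 77% |
| 0.7 | 0.60 | 0.51 | 15% | 3.08 / 3.34 | 86% / 91% |

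At r = 0.5 the difference detectable with 80% power falls from 0.78 to 0.67 SD. These figures concern the interaction contrast that section 2.15 emphasises; the article does not specify the form of the post hoc tests.

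**Missing visits.** At 10% dropout, 90 × 0.10 = 9 patients are incomplete and 81 are complete. Deleting incomplete patients therefore leaves 81, against a planned minimum of 80. What a mixed model recovers depends on how many of the 9 have a week-4 or week-16 value, and the article gives no split. The range is 0 to about 9.

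**Simulation (30 per arm, assumed mechanisms).**
- With 10% random dropout and r = 0.5, the SD of the week-16 estimate was 0.279 with deletion, 0.275 for the mixed model with free baseline means, and 0.241 with a common baseline mean. Nearly all the gain comes from handling baseline.
- With dropout after week 4 made more likely by a high week-4 score (about 82 completers), a true week-4 effect of −0.50 was estimated at −0.44 to −0.47 with deletion and −0.50 by the mixed model. At week 16 the two were almost the same (for example −0.488 and −0.486 at r = 0.5).

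**The case against.** The strongest reply is that linear mixed models are named first, and that the parenthesis may only describe the layout: one within-patient factor and one between-group factor. On that reading nobody with a usable visit is dropped, and the handling of incomplete patients can be left to an analysis plan that is not shown. This stands as far as it goes. A reader might infer that the plan is a completer analysis that discards 9 of 90 patients. The article does not say so: deletion depends on the procedure, none is named, and the number of patients with only one follow-up visit is unknown. Nor does deletion at 10% harm planned power, since 81 remain. What survives is that the text permits an analysis at odds with its own intention-to-treat statement.

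A second reply is that the change-score contrast is valid and matches the interaction for which the trial was sized. That is also right. A reader might infer that the planned test is biased or that baseline information is wholly thrown away. Neither follows: randomisation keeps the contrast unbiased, and a change score already uses baseline in part. The loss is the further 15% to 35% of variance, and it is smallest where the correlation is high.

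Third, the condition that the interaction be significant is the only protection that section 2.15 states across the pairwise comparisons. Removing it without a replacement would leave three comparisons, two follow-up visits and two primary outcomes uncontrolled. This objection stands in full and shapes the fix.

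**Conclusion.** The point holds as one of efficiency, together with a wording ambiguity. The planned contrasts are unbiased, but their variance is 1.54, 1.33 or 1.18 times what baseline adjustment would give at r = 0.3, 0.5 or 0.7 (1 divided by 0.65, 0.75 and 0.85). Power for 0.65 SD with 27 per arm is lower by about 18, 12 or 5 percentage points. This rests on the assumed correlations, equal SDs across visits and an illustrative effect; the direction does not depend on the particular values of r and the effect used.

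The data-loss part is conditional. It matters only if the ANOVA label is acted on, it affects 0 to about 9 of 90 patients at the planned dropout, and its harm lies in possible bias and departure from intention-to-treat rather than in planned power. Bias needs dropout related to response. The exclusion events in section 2.12 make that possible, but the article does not say whether excluded patients are still measured.

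**What to change.** 1. Delete the words two-way mixed ANOVA from section 2.15 and name one likelihood-based linear mixed model (SPSS MIXED, REML, unstructured covariance) that uses all available data from the randomised patients.
2. Handle baseline in one of two ways. Either model weeks 4 and 16 with group, visit, group-by-visit, baseline and baseline-by-visit, or keep week 0 as an outcome and constrain the groups to a common baseline mean. The second form also keeps patients with no follow-up value in the model; the first omits them.
3. Take the group effects from this model and report A-B, A-C and B-C with 95% confidence intervals at each follow-up visit. All three comparisons are already planned, so none should be dropped.
4. Keep an overall test that must be significant before the pairwise comparisons are interpreted, or replace it with a stated multiplicity rule.

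The cost is small: same data, visits and software, and section 2.13 says that the trial had not started. There is one real downside. The primary test would no longer match exactly the interaction test behind the sample size in section 2.14, and that section should say so.

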### 2.9. Outcomes

The evaluations will take place at all time-points: before the treatment sessions (week 0), after ten treatment sessions (week 4), and four months after the beginning of the trial (week 16). The primary outcomes will be: functional disability (NDI) [25] and pain (VAS) [26]. Several secondary outcomes will also be evaluated: cervical range of motion (CROM) [27], craniovertebral angle (CVA) [28], Nijmegen Questionnaire (NQ) [29,30], Hi-Lo test [31], breath holding time (BHT) [32,33], single breath count (SBC) [34], end tidal CO_2_ (ETCO_2_) [35] and respiratory rate (RR) [36], chest wall expansion (CWE) [37], the Hospital and Anxiety Depression Scale (HADS) [38], the Tampa Scale for Kinesiophobia (TSK) [39] and adverse events [40]. All outcomes are briefly presented below. The corresponding references for each of the above outcomes include reliability and validity details, except for some further testing proposed in Section 2.10 and Section 2.11.

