#### 2.9.2. Secondary Outcome Measures

Range of motion (ROM) [27]: A smartphone-based application (iHandy Level: https://play.google.com/store/apps/details?id=com.ihandysoft.carpenter.level.free&hl=et&gl=US (accessed on 10 May 2022)) downloaded to a smartphone (Model P30/ELE-L29, Huawei Smartphone, China 2019, purchased January 2021), in parallel with a sensor-based commercially available device (KFORCE SENS electronic goniometer, KINVENT-France), will be used to accurately measure ROM during neck movements of flexion-extension, left-right side flexion, and left-right rotation. 

Craniovertebral Angle (CVA) [28]: Lateral photography examination of the FHP through lateral photographs can provide very reliable estimates. FHP will be estimated in a relaxed sitting position for all participants. A smartphone-based application (Forward Head Posture-FHP app), available on Google Play (https://play.google.com/store/apps/details?id=com.ysjworld.fhp&hl=en&gl=US (accessed on 10 May 2022)), will be used for CVA angle measurements.

Nijmegen Questionnaire (NQ) (Greek version 2014) [29]: Screening tool used to detect patients with hyperventilation complaints and DB patterns. Scores > 19 are used as the cut-off score to separate hyperventilatory patients from normal subjects [30]. NQ values in healthy individuals range from 10 to 12 ± 7, and values have been observed to decrease towards these levels in subjects with DB after breathing retraining [30].

Hi-Lo test [31]: The examiner will be given instructions on how to conduct and record results from the Hi-Lo test, including the following: “Examiner at the front and slightly to the side of the individual has to place one hand on the patient’s sternum and the other hand on their upper belly. The examiner must evaluate if and to what extent abdominal or thoracic motion predominates while breathing. Additionally, paradoxical breathing needs to be considered, as well as the degree of abdominal or thoracic breathing rate.” This test evaluates DB.

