### 2.10. Respiratory Outcomes Validity Investigation in Patients with NSCNP

#### 2.10.1. Construct Validity of the NQ 

The assessment of the construct validity of the NQ will be performed via exploratory factor analysis, similar to its previous validation in a population with asthma [29], to examine the factor structure of the NQ in a population with NSCNP. This study has not been performed in a population with chronic pain and without a respiratory condition, such as the one under study.

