#### 2.10.2. Concurrent Validity of Respiratory Outcomes Assessing DB

The examination of relationships between the following respiratory outcomes of DB (concurrent validity) will be performed: the NQ (psychophysiological dimension), ETCO_2_ (biochemical dimension), and RR, Hi-Lo, BHT, SBC, CVA, CWE (biomechanical dimension). Similar research has previously been conducted [41], but not in a population with NSCNP.

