#### 2.10.3. Prevalence of DB in Patients with NSCNP

As there are no established reference standards for DB [33], the diagnostic accuracy of respiratory measurements relating to DB in patients with NSCNP cannot be examined. Instead, as previously proposed [42], the prevalence of DB in patients with NSCNP can be presented, using cut-off scores established from previous studies performed in an asymptomatic population without a respiratory condition (ETCO_2_ with a cut-off score of 35 mm Hg, the NQ with a cut-off score of 19), and the Hi-Lo test, for the determination of the type of breathing, as single or combined (in pairs, or using all three) outcomes, to identify the percentage of the population with NSCNP that exhibits respiratory dysfunction. 

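### Pearson correlation is fixed for every concurrent-validity measure, including the Hi-Lo test, which is described mainly as a breathing type without a score; secondarily, the NQ factor analysis is to be run by principal components

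*Protocol article*

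**What the plan says.** **Concurrent validity.** Objective 3 of the protocol article covers construct and concurrent validity of the respiratory measures of dysfunctional breathing. Section 2.10.2 lists what is to be related: the NQ, end-tidal CO2, and the group "RR, Hi-Lo, BHT, SBC, CVA, CWE (biomechanical dimension". That makes eight measures. Section 2.15 names one method for them, with no exception: Pearson's "bivariate correlations will be employed for the examination of concurrent validity of respiratory outcomes".

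**Hi-Lo.** Section 2.9.2 defines the test as an examiner's judgement: "The examiner must evaluate if and to what extent abdominal or thoracic motion predominates while breathing". It adds that "paradoxical breathing needs to be considered, as well as the degree of abdominal or thoracic breathing rate". No score, range or coding follows. Section 2.10.3 gives numeric cut-offs for end-tidal CO2 and the NQ, but uses Hi-Lo differently: "and the Hi-Lo test, for the determination of the type of breathing". Section 2.9 also lists Hi-Lo among the secondary trial outcomes. The only model that section 2.15 names for the trial comparison is a two-way mixed ANOVA, and the outcomes it covers are not listed.

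**NQ.** Section 2.10.1: "The assessment of the construct validity of the NQ will be performed via exploratory factor analysis". Section 2.15: "The principal components analysis method will be performed for the factor analysis of the NQ".

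**The concern.** Pearson's coefficient treats the numbers it is given as measurements on a line. A breathing type has no such numbers until someone assigns them. Abdominal and thoracic predominance can be seen as two ends of one scale, but paradoxical breathing has no evident place on it. The plan therefore fixes the method while leaving the scale open, and its own description of the test allows the case in which the method fails. A Hi-Lo correlation could then look weak or moderate according to how the data sheet was coded, and be read as evidence about validity.

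For the NQ, construct validity concerns the variance that items share. Principal components analyses total variance, so each item's unique variance and error enter the loadings. Loadings and explained variance are the figures that would be used to describe the structure, and both would be too high.

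**Working it through.** The plan gives no figure on this point, so there is nothing to reproduce. The checks below show the mechanism. Shares, means and loadings are assumptions; none comes from the protocol.

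**1. How many correlations are touched.** Eight measures (section 2.10.2) give 8 × 7 / 2 = 28 pairs. Hi-Lo is in 7 of them; 28 − 7 = 21 do not involve it.

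**2. Three unordered types.** Let p be the shares of the types, μ the means of the other measure in within-type SD units, and c the codes, with a bar for the p-weighted mean.

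- r = Σp(c − c̄)(μ − μ̄) / √{Σp(c − c̄)² × [1 + Σp(μ − μ̄)²]}
- coding-free correlation ratio: η = √{Σp(μ − μ̄)² / [1 + Σp(μ − μ̄)²]}

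Example: shares 0.3/0.5/0.2 (abdominal/thoracic/paradoxical), means 0/−0.8/−0.4. Then μ̄ = −0.48, Σp(μ − μ̄)² = 0.1216 and η = √(0.1216/1.1216) = 0.33.

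- Codes 0,1,2: −0.128 / √(0.49 × 1.1216) = −0.17
- Codes 0,2,1: −0.304 / √(0.76 × 1.1216) = −0.33
- Codes 1,0,2: +0.176 / √(0.61 × 1.1216) = +0.21

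| Shares | Means | r, codes 0,1,2 | r, codes 0,2,1 | r, codes 1,0,2 | η |
|---|---|---|---|---|---|
| 0.3/0.5/0.2 | 0/−0.8/−0.4 | −0.17 | −0.33 | +0.21 | 0.33 |
| 0.4/0.4/0.2 | 0/−0.5/−0.8 | −0.30 | −0.21 | −0.04 | 0.30 |
| 1/3 each | 0/−0.8/0 | 0.00 | −0.31 | +0.31 | 0.35 |

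Part of the change of sign is plain reversal of the scale, which is harmless. To remove it, keep thoracic coded above abdominal by replacing 1,0,2 with its mirror 1,2,0, which reverses the sign of r. The rows then read −0.17, −0.33, −0.21; −0.30, −0.21, +0.04; and 0.00, −0.31, −0.31. The size still depends on where paradoxical breathing is placed, and in the second row so does the sign, though by a small amount.

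**3. Two types.** In one simulated data set of 90, recoding left r at 0.220 apart from its sign, and its p-value equalled that of the t-test (0.0375 for both). This is the point-biserial correlation.

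**4. Graded score.** With a fixed three-level score unrelated to the other measure, n = 90 and 20,000 runs, Pearson rejected at the 5% level in 0.051 of runs. The test keeps its level; the coefficient is approximate because equal spacing of the grades is assumed.

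**5. Principal components.** For k items with a common true loading λ on one factor, the component loading is √{[1 + (k − 1)λ²] / k}. With k = 4 and λ = 0.55: √(1.9075/4) = 0.69. With k = 5: √(2.21/5) = 0.66.

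For an assumed 16 items in three uncorrelated clusters of 6, 5 and 5:

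| True loading | Component loading | True variance explained | Variance explained by components |
|---|---|---|---|
| 0.5 | 0.61–0.63 | 25% | 39% |
| 0.6 | 0.68–0.70 | 36% | 48% |
| 0.7 | 0.76–0.77 | 49% | 59% |

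Loadings rise by about 0.06 to 0.13 and explained variance by about 10 to 14 points. Three eigenvalues exceed 1 in each case, so the number of dimensions is recovered.

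**The case against.** The strongest defence is that a three-type nominal code is nowhere stated. Section 2.9.2 also asks for extent and degree, which points to a grade, and the prevalence use in section 2.10.3 would work with a two-way result. In either case Pearson does little or no harm, and a point-biserial analysis is Pearson's r on a 0/1 code. This stands, and it makes the finding conditional. It does not remove it, because the article names a specific method for a measure whose scale it leaves open.

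On the NQ, section 2.15 presents principal components as the way the factor analysis will be done, a common if loose usage. Section 2.10.1 also models the analysis on a previous validation in asthma; if that study used components (its method is not given here), a change of extraction could cost comparability. This stands as a reason to report components alongside.

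A reader might infer more than the document supports:

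- *That the mixed ANOVA is prescribed for Hi-Lo and for adverse events.* Section 2.15 does not say which outcomes the model covers, and a condensed article may leave categorical outcomes and safety tables to the full plan. For adverse events the reading is also implausible, since section 2.9.2 rates them during and after treatment and so gives no baseline for a group-by-time model.
- *That validity will be judged by p < 0.05.* Section 2.15 sets a general 5% level and does not make significance the criterion of validity.
- *That the validity results would be uninterpretable.* The 21 pairs without Hi-Lo are not touched by the coding problem, and components inflate the NQ loadings without destroying the structure.

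**Conclusion.** The point holds, conditionally, and is minor. Section 2.15 applies Pearson without exception to a set that includes Hi-Lo, which is described mainly as a breathing type and has no stated score. If three or more unordered types are recorded, 7 of the 28 correlations are coding-dependent; in the assumed examples, with thoracic kept above abdominal, r ranges from −0.17 to −0.33, from −0.30 to +0.04, and from 0.00 to −0.31. If Hi-Lo is binary there is no error; if it is graded, Pearson is an approximation. These sizes rest on assumed shares and means and illustrate the mechanism; they do not predict the trial's results.

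The principal components point is real but modest: it fits poorly with the promised exploratory factor analysis and overstates loadings and explained variance. Neither point affects the primary outcomes (NDI and pain VAS).

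**What to change.** - **State the Hi-Lo scoring**: the categories or grades, and where paradoxical breathing falls.
- **Match the method for the 7 Hi-Lo pairs to that scoring.** For types, compare the other measures across breathing types (ANOVA or Kruskal–Wallis with eta-squared). For abdominal versus other, use the point-biserial correlation. For grades, use a rank correlation.
- **If Hi-Lo is compared between trial arms**, use a categorical repeated-measures model (mixed logistic or GEE) rather than the mixed ANOVA.
- **Align sections 2.10.1 and 2.15 on the NQ**: use a common-factor extraction (principal axis or maximum likelihood), and report principal components alongside if needed for comparability with the earlier validation.

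The cost is wording and slightly more analysis work. No further measurements are needed beyond those already planned, and section 2.13 says that the trial had not started when the article was written.
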